## Abstract

Supplemental Digital Content is available in the text

Article SummaryStrengths and limitations of this studyThe web-based design of the study will allow efficient, low cost data collection during the time of an international health care crisis.The survey is translated to more than 10 languages which will allow comparisons between many countries affected by the pandemic.Anonymous web-based surveys are prone to bias, but it is extensively discussed in the protocol how this bias will be managed during data analysis.The study protocol invites pregnant women to provide their personal information for participation in future research. This provides an opportunity for follow up of the participants.

## Introduction

1

Anxiety is a feeling of worry, nervousness, or unease about something with an uncertain outcome and it can co-exist, predispose or cause depression.^[1]^ The unpredictability of the coronavirus disease 2019 (COVID-19) pandemic makes people prone to severe anxiety.^[2]^ Research has shown that pregnant women are especially prone to anxiety^[1,3]^ with prevalence of gestational anxiety between 15% and 23%,^[4]^ in comparison with 3 to 5% of anxiety symptoms in the general population.^[5]^

Risk factors for anxiety are similar in the general population and during pregnancy, including bad childhood experiences (overprotective or harsh parenting, maltreatment, and physical punishment). Parental history of mental disorders and low socioeconomic status have also been described to increase the risk of anxiety.^[2,5,6]^

About 10% of pregnant women experience perinatal depression globally.^[7–10]^ Untreated perinatal depression may result in adverse obstetric outcomes and is a risk factor for poor maternal health, inadequate prenatal care, and postnatal depression.^[10,11]^ In addition to the potential negative impact on pregnancy outcomes, perinatal depression is associated with disrupted maternal-infant bonding, increased irritability, and decreased activity. Children born to depressed mothers are at risk for delayed cognitive and language development, lower IQ, and increased prevalence of psychiatric and emotional problems. Depression that begins during pregnancy frequently continues or worsens after delivery.^[7,9,12]^

Mothers have a strong desire to provide their children with a stable environment, however, the situation of the growing pandemic with strict limitations regarding social contacts and economic instability does not make a secure situation for procreation.^[5]^ Based on the current data, it seems that the severe acute respiratory syndrome coronavirus 2 (SARS-CoV-2) does not cause a severe course of infection in pregnant women as they are usually young and without co-morbidities.^[6]^ It is worth to underline that the COVID-19 pandemic is not only a public health crisis but also a social, demographic and economic one and it has a substantial negative psychosocial effect on everyone, including pregnant women. The resulting anxiety of pregnant women has a negative impact on pregnancy, such as increased risk of preeclampsia, depression, nausea, vomiting and could even cause preterm labor or miscarriage.^[1]^ What is more, maternal anxiety may lead to adverse effects of the newborns, like low birth weight, growth restriction or low APGAR score.^[13,14]^

The primary aim of our study is to compare differences in anxiety and depression scores of pregnant women between countries affected by the COVID-19 pandemic. The secondary aim is to assess demographic, economic, and social aspects affecting maternal anxiety and depression scores among pregnant women worldwide in the time of the COVID-19 pandemic. Finally, we will be able to compare differences in perception of the different aspects of the pandemic (social distancing, restrictions related to delivery) between countries and according to the epidemic status (number of infected patients, number of reported deaths). The comparisons will also be done according to the COVID-19 status of the participants.

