#### Data collection

2.1.10

The Pregmind International Research Group was formed, and a website was constructed for the international promotion of the study (www.pregmind.org).^[28]^ Data collection will begin with an initial social media post created on the the Pregmind Facebook fan page. The post will be prepared in the predefined languages and shared publicly. Campaigns will be set up to promote the study. Advertisements and posts will be shared on pages targeted towards pregnant women on every continent in the world in the predefined languages. We will also target closed pregnancy orientated groups via private messages on Facebook and invite them to post the study advertisement with the link to the survey on their pages.

The recruitment target will be reached when the desired sample size per region is achieved. We hope to collect data from at least one country from every continent. The survey will be translated into 15 languages, out of which 4 (English, Spanish, Chinese, Arabic) are widely spoken around the world and are not nationality related. For this study, the recruitment rate is difficult to predict. We expect data collection to take place at least six months for each language, based on similar previous studies of mental health.^[29]^ Recruitment rates may vary in different regions. Recruitment will not start simultaneously for all regions.

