#### Statistical analysis

2.1.11

Data will be kept anonymous and non-identifiable. For the statistical, analysis, R software^[30]^ and the Mplus computer program will be used.^[31]^ Data collection will include the most relevant demographic variables allowing us to compare collected data within a population. Reweighting and other techniques will allow adjustment for known or expected discrepancies between sample populations.^[32]^ To ensure comparability reweighting techniques, measurement invariance analysis will be performed. For the reweighting, we will use procedures suggested by Gelman and Carlin.^[32]^ We will collect external information about the distribution of age, place of residence, education level of pregnant women in the population, and adjust our sample to match the proportion in each country. If this is not possible because of the shortage of data, we will use propensity score matching^[33]^ and regression technique to balance the groups’ demographic distributions and make comparisons justifiable. Additionally, to ensure a valid comparison between countries, we will conduct a detailed measurement invariance analysis.^[34]^ Furthermore, we plan to perform regression analyses to explore potential associations between the reported anxiety, depression levels, and medical, sociodemographic, and pandemic related variables (including burdens related to social distancing). Altogether there will be 30 different variables. According to a rule of thumb “N > 104+m”, where N is the number of participants and m is the number of variables, the sample size will allow us to perform all planned analysis.^[35]^ Our main variables (GAD-7 and PHQ-9 scale) are measured by multiple indicators (questions), this opens the possibility to use Confirmatory Factor Analysis (CFA). This technique will allow us to assess the comparability of variables and, if necessary, address the problem of comparability using different latent variable modeling strategies.^[34]^ Principal analysis will be conducted using Structural Equation Modeling Framework which allows us to account not only for comparability problems but as well for measurement error.^[36]^

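### Epidemic status is given as absolute numbers of infected patients and deaths, so a cross-country comparison on it would partly reflect country size

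*Protocol article*

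**What the plan says.** The last paragraph of the Introduction sets three aims in order. The primary aim is to "compare differences in anxiety and depression scores of pregnant women between countries affected by the COVID-19 pandemic". The secondary aim concerns demographic, economic and social influences on those scores. The third aim turns to how women perceive the pandemic and its constraints, and these perceptions are to be set against each other "between countries and according to the epidemic status (number of infected patients, number of reported deaths". The paragraph closes with a comparison by the participants' own COVID-19 status.

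The parenthesis in the third aim is the only place where the article says what epidemic status means. Section 2.1.11 (Statistical analysis) speaks only of "medical, sociodemographic, and pandemic related variables (including burdens related to social distancing") as regression covariates and does not return to the definition.

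Two statements in section 2.1.10 (Data collection) bear on the point: "We hope to collect data from at least one country from every continent", and "Recruitment will not start simultaneously for all regions". The same section expects collection to last at least six months for each language.

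**The concern.** The two quantities named are totals. At equal epidemic intensity, a country with ten times the population reports ten times the total. With recruitment meant to span continents and 15 survey languages, similar population sizes across the participating countries are unlikely. An association between perceptions and the raw count could then reflect something that goes with country size, and a real gradient with intensity could be weakened, hidden or reversed.

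Timing adds a second difficulty. Regions start at different dates and stay open for months, so a total without a date also depends on when a woman happened to answer.

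At stake is how the epidemic-status part of the third aim is interpreted.

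**Working it through.** **The plan's own figure.** The article states no figure for this comparison. Its only calculation is the sample size in section 2.1.9, which does not use epidemic status. It reproduces from the two-sample formula for means, with 80% power and 0.05 taken as two-sided (the article does not state sidedness):

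- GAD-7: difference 0.20 × 4.75 = 0.95, SD 4.76, gives 395 per country (stated: 394).
- PHQ-9: difference 0.20 × 5.2 = 1.04, SD 5.06, gives 372 per country (stated: 372).

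Nothing below changes these numbers.

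**Step 1: what a count contains.** Count = population × rate, so log(count) = log(population) + log(rate). Comparing countries on the count compares them on the sum of both terms.

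**Step 2: when two countries change places.** Let the smaller country have population P and rate a, and the larger have population R × P and rate b, with R > 1.

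- The smaller country is the more intensely affected when a/b > 1.
- The larger country has the higher count when R × P × b > P × a, that is, when a/b < R.
- The two rankings therefore disagree exactly when 1 < a/b < R. If a/b is below 1, the larger country leads on both measures and nothing reverses. If a/b exceeds R, the smaller country leads on both.

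**Step 3: an example.** The article gives no populations or rates, so these are assumptions.

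- Smaller country: 5,000,000 × 200/100,000 = 10,000 cases.
- Larger country: 50,000,000 × 40/100,000 = 20,000 cases.
- R = 50/5 = 10 and a/b = 200/40 = 5, which lies between 1 and 10, so the rankings disagree. The larger country has 20,000/10,000 = 2 times the count at 40/200 = 0.2 times the rate.

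**Step 4: how much of the count is size.** Assume that log10 population and log10 rate vary independently and normally between countries, with SDs from 0.3 to 0.7. The share of the variance of log count due to population is SDpop² / (SDpop² + SDrate²). The rank correlations come from simulation with 200,000 draws per setting.

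| SD log10 population | SD log10 rate | Variance share due to population | Spearman, count with population |
|---|---|---|---|
| 0.3 | 0.7 | 0.09/0.58 = 16% | 0.38 |
| 0.5 | 0.5 | 0.25/0.50 = 50% | 0.69 |
| 0.7 | 0.3 | 0.49/0.58 = 84% | 0.91 |

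The other settings tried fall between the outer rows. Dividing by population removes the log(population) term. Under the same independence assumption, the expected rank correlation with country size is then about 0.

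**Step 5: whether another part of the plan removes the problem.** The reweighting in section 2.1.11 uses the "distribution of age, place of residence, education level of pregnant women in the population". These are characteristics of respondents. Reweighting, or the matching and regression named as its fallback, changes who stands for a country but not the number of cases attached to that country. Measurement invariance and factor analysis concern the GAD-7 and PHQ-9 items. None of them standardises a country-level count.

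**The case against.** The strongest reply is that a parenthesis in an aims paragraph is not an operational definition. It may be shorthand for two kinds of surveillance data, with scaling, window and source left to an analysis plan that is not shown. Case and death figures are external to the survey, so they can be scaled at analysis without loss of data. This is a fair reason to keep the point small. It does not remove it, because the article does not merely leave the measure open: it names one, and the one named is unsuitable across countries of different size.

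Three stronger readings are tempting and are not supported:

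- A reader might infer that small, heavily affected countries will be classed as low and large, lightly affected ones as high. The article describes no high/low split and no ranking, so misranking is a possibility for some pairs of countries and not a stated outcome.
- A reader might infer that the third aim cannot be answered. The same sentence lists comparison between countries separately, and the next adds comparison by the participant's own COVID-19 status. Neither depends on the count.
- A reader might infer that the main results are compromised. The primary comparison of GAD-7 and PHQ-9 scores is between countries, not by epidemic status.

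The fact that reported cases depend on testing is true of counts and rates alike. It is a caveat on reported cases in either form, not an argument for preferring rates.

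A comparison over time within one country would escape the size problem, since population is nearly constant there, but the article describes none.

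**Conclusion.** The point holds as a minor one. Taken as written, the measure of epidemic status mixes country size with epidemic intensity in a cross-country comparison, and nothing else in the article separates them. The direction follows from arithmetic. The size does not follow from the documents: the 16% to 84% share and the 0.38 to 0.91 correlations rest on assumed spreads and on independence of population and rate, and the two-country example on assumed populations and rates. The reach is limited to the epidemic-status part of the third aim. If the full plan already uses population rates over a dated window, only the wording of the article needs to change.

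**What to change.** Replace the parenthesis in the aims with a definition such as: reported cases and reported deaths per 100,000 population in the woman's country of residence, over a stated window ending at the date of her response. State the length of the window and the data source before analysis. The window is needed as well as the denominator, because with staggered recruitment a per-capita figure without a date would still mix intensity with calendar time. Add a sentence that reported cases depend on testing. The documents give no basis for making one of the two measures the main one, so that choice is the investigators' to make and state. Use regional figures only if the place-of-residence item in the survey identifies the region. The article does not show how detailed that item is.

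The cost is one line of wording and published population figures. The case and death figures are needed for this aim in any event, and country is needed for the primary aim. The one assumption is that the survey tool records the submission date, which the article does not mention. The sample size and the primary analysis stay as they are.

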## Methods and analysis

2

### Study design

2.1

This is a cross-sectional study. Data will be collected through an anonymous web-based survey made up of closed questions with multiple choice answers. The survey has three parts:

1)questions related to general demography, pregnancy health history, mental health history, socioeconomic factors, as well as perception of fear, burden and restrictions related to the COVID-19 pandemic and2)General Anxiety Disorder-7 (GAD-7) questionnaire for anxiety assessment3)Patient Health Questionnaire–9 (PHQ-9) for depression assessment.

#### Survey development

2.1.1

The survey will be conducted using the Research and Electronic Data Capture (REDCap) tool. It is a secure application that provides an interface for data entry.^[15,16]^ All data will be collected anonymously, and the answers will not be attributed to a specific individual.

The survey has been developed by a multidisciplinary team comprised of physicians, midwives, psychologists, and sociologists. All experts have proposed questions from their field. The questions, in turn, have been reviewed by a second group of field experts. The second group of experts also proposed questions, and their feedback has been included in the final version of the survey. A pilot study was performed on ten Polish, Chinese and English-speaking pregnant women, and their feedback was obtained to enhance the readability and the content of the survey. In the following stage of the study, this will be done for all participating languages.

#### Description of the survey

2.1.2

The survey collects information on demography, socioeconomic situation, general health history, pregnancy risk assessment, mental health history, and specific aspects related to the COVID-19 pandemic. Both GAD-7 and PHQ-9 scales are used to assess anxiety and depression. The survey consists of 60 questions, and it has the following structure: screening questions, consent form, demographic and socioeconomic questions, mental health history questions, general health history questions, pregnancy risk assessment questions, COVID-19 specific questions, and the GAD-7 and PHQ-9 scales. Supplemental Digital Content (Appendix 1. Full survey in English)

#### Screening questions

2.1.3

The survey has 6 screening questions, of which the first asks if the woman is pregnant or not. It is followed by questions regarding last menstrual period and estimated date of delivery, type of provided care (midwife, doctor, shared, none), and if the pregnancy has been confirmed by a medical professional. This is aimed at decreasing bias created by women claiming to be pregnant to complete the survey.

Demographic and socioeconomic questions ask about place of residence, education, number of people in household, sources of income, marital status, and family/partner support. Pregnancy risk assessment questions include parity, previous mode of delivery, pre-pregnancy chronic diseases, pregnancy-related complications, and infertility treatment. Mental health history questions cover pre-pregnancy and current mental health issues. COVID-19 specific questions cover fear and burden related to COVID-19 pandemic and the restrictions imposed in order to limit the spread of the virus.

#### Consent form

2.1.4

Once participants are deemed eligible to participate, a consent form appears that explains the purpose of the study, what the data will be used for, how the data will be stored, requirements of the participant, and any potential benefits or risks incurred by participating, and that consent for participation can be withdrawn at any point before submission of the questionnaire. Because of the questionnaire's anonymous nature, the participant information cannot be withdrawn after data has been submitted. The researchers will not know which data belong to which participant. Participants will be informed of this in the consent form.

#### GAD-7 scale

2.1.5

Generalized Anxiety Disorder 7-item (GAD-7) questionnaire measures the severity of anxiety over the past two weeks. The GAD-7 questionnaire is a 7-question scale. There are four choices regarding the severity of symptoms: “not at all”, “several days”, “more than half the days” and “nearly every day”, which correspond to 0, 1, 2, and 3 points score, respectively (minimum total score 0, maximum 21).^[17]^ The summarized score is used to assess anxiety intensification. The scale is commonly used to diagnose generalized anxiety disorder in the general population. National Institute for Health and Care Excellence (NICE) recommends using this tool as a measurement of prenatal anxiety.^[18]^ The GAD-7 scale is the only scale besides the State-Trait Anxiety Inventory (STAI) that is validated for women in the prenatal period.^[4]^ The advantages of the GAD-7 scale are that it is more straightforward, easy to complete and that the interpretation is easier with fewer questions: 7 in GAD-7 vs. 20 in STAI. Moreover, the GAD-7 scale is available without cost and is easier to use on social media. In the general population a score of ≥ 10 allows diagnosis of generalized anxiety disorder.^[19]^ Nevertheless, in pregnant women, the cut-off point has been established as ≥7 with a sensitivity of 73.3% and specificity of 67.3%.^[20]^ (Table 1)

**Table 1 T1:**
[figure not shown]
GAD-7 and PHQ-9 scale – anxiety and depression.

#### PHQ-9 scale

2.1.6

NICE also recommends using the PHQ-9 scale with the GAD-7 scale to measure the depression risk in pregnant women.^[18]^ PHQ-9 has a similar grading system to GAD-7 and consists of nine questions exploring the depression symptoms over the past two weeks with four possible answers: “not at all,” “several days,” “more than half the days” and “nearly every day,” which correspond to 0, 1, 2, and 3 points score, respectively (minimum total score 0, maximum 27).^[21]^ According to American College of Obstetricians and Gynecologists (ACOG), Edinburg Postnatal Depression Scale (EPDS) and PHQ-9 are appropriate tools to measure antepartum depression.^[22,23]^ The advantage of the PHQ-9 scale is that it has fewer questions: 9 questions vs 20 in EPDS. Participants that achieve a score of ≥ 10 meet diagnostic criteria of perinatal depression.^[24]^ (Table 1)

#### Follow-up, disclaimers and data storage

2.1.7

After completing the questionnaire, women will be given the option of providing their contact information (first name and email address). This database of contacts will be used to update participants on the results of this study and invite them to future studies and activities. Neither the women who participate in giving their data nor those that provide contact information in the study will receive any compensation. This study has received no funding and is a non-profit initiative of an international perinatal medicine community to better understand the burden of COVID-19 pandemic on maternal mental health worldwide. Contact information will be collected using a separate form so that personal information cannot be linked to the data provided in the web-based survey.

In the consent section of the survey, participants will be warned that some questions might be of a sensitive nature, and they can skip any question that they do not feel comfortable answering. The only parts of the survey that need to be fully answered are the GAD-7 and PHQ-9 scale.

All data will be stored on secure internal servers at the St. Sophie's Obstetrics and Gynecology Hospital, Warsaw, Poland, and will be directly downloaded from the REDCap tool and stored on a password-protected computer in a locked room at the Department of Reproductive Health of the Centre of Postgraduate Medical Education located on the hospital grounds. Data will be stored in this location for 3 years before it is destroyed. Principles outlined in the Data Protection Act are considered to ensure proper handling of the collected personal data.

